### Outcome variables

All efficacy and laboratory outcomes were measured at baseline, 3 months post-intervention and after a further 9 months follow-up. Data related to infectious morbidity and hospitalisation were collected weekly during the intervention period and monthly during the follow-up period. Serious adverse events were measured at any time. The primary time-point of interest for all outcome variables is at the end of the intervention.

The primary outcome of the study is cognitive development, as measured using the cognitive composite score of the Bayley Scales of Infant and Toddler Development, Third Edition (Bayley III)
^
7
^. Bayley-III is a validated index of child development and the preferred field assessment tool. It is a standard series of measurements primarily to assess cognitive, motor (fine and gross) and language (receptive and expressive) development of infants and toddlers aged 0–3 ½ yrs. The total number of credited items is converted into scaled scores based on child’s age, which are then converted to composite scores of each subscale.

Key secondary outcomes include motor and language composite scores assessed by Bayley III, growth (length-for-age z-score, weight-for-age z-score), and laboratory indices (haemoglobin and ferritin concentrations). Secondary outcomes include other anthropometry measures (weight-for-length z-score, stunting, wasting, underweight, head circumference) and haematological and iron diagnoses (anaemia, iron deficiency, iron deficiency anaemia). Anthropometry outcomes (z-scores) will be derived using the child’s length and weight together with age and sex of the child according to age and sex specific WHO international reference growth standards
^
8
^. Using the z-scores, stunting will be defined as length-for-age z-score <-2, underweight as weight-for-age z-score <-2, and wasting as weight-for-length z-score <-2. Using the child’s haemoglobin (g/L), ferritin (µg/L), and C-reactive protein (mg/L), anaemia will be defined as haemoglobin <110 g/L, iron deficient as ferritin <12 µg/L or ferritin <30 µg/L if C-reactive protein >5 mg/L, and iron deficient anaemia as iron deficient and anaemia.

Exploratory outcomes include child’s behaviour using items from the Wolke’s Behaviour rating scale
^
9
^, consisting of nine behaviours each scored on a nine-point scale with higher scores indicating more favourable behaviour, and the temperament questionnaire
^
10

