### Multiple testing adjustment

The two primary comparisons of interest for the primary and key secondary outcomes are iron versus placebo and MNPs versus placebo. We will use a Bonferroni adjustment combined with a gatekeeping procedure to ensure control of the Type I error rate for the primary outcome across all three pairwise comparisons. Using the Bonferroni correction, we will test each of the two primary null hypotheses of no difference between iron and placebo and MNPs and placebo for the primary outcome at the two-sided 2.5% level of significance. If at least one of the two primary null hypotheses can be rejected (multiplicity unadjusted P-Value < 0.025), a comparison of iron versus MNPs will take place at either the two-sided 2.5% (if either iron or MNPs is superior to placebo) or 5% level of significance (if both iron and MNPs are superior to placebo). Estimates and two-sided confidence intervals will be presented with the same level of significance as used for the testing of these null hypotheses, along with multiplicity unadjusted and adjusted P-Values. If neither iron nor MNPs is superior to placebo, we will report the estimate and two-sided 95% confidence interval but not the P-Value for the comparison of iron versus MNPs.

For the set of key secondary outcomes, we will use the Hochberg procedure for each of the three pairwise comparisons at the level of significance used for the primary outcome only if the corresponding null hypothesis is rejected for the primary outcome. No multiplicity adjustment is planned for secondary and exploratory outcomes, and no P-Values will be presented.

We will follow the above outlined multiple testing approach for the primary and key secondary outcomes both for the primary time-point at month 3 and the secondary time-point at month 12 separately. The primary objective of the trial will have been met if one of the two primary null hypotheses for the primary outcome at the primary time-point can be rejected at the predetermined significance level. 

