Change in haemoglobin concentration (g/L)	XXXX	X.X (X.X)	XXXX	X.X (X.X)	XXXX	X.X (X.X)	X.X (X.X to X.X)	0.XXX	0.XXX	X.X (X.X to X.X)	0.XXX	0.XXX	X.X (X.X to X.X)	0.XXX	0.XXX
Ferritin (µg/L)	XXXX	XX.X (XX.X- XX.X)	XXXX	XX.X (XX.X- XX.X)	XXXX	XX.X (XX.X- XX.X)	X.XX (X.XX to X.XX)	0.XXX	0.XXX	X.XX (X.XX to X.XX)	0.XXX	0.XXX	X.XX (X.XX to X.XX)	0.XXX	0.XXX
Secondary variables															
Anthropometric indices															
Stunting	XXXX	XX (X.X%)	XXXX	XX (X.X%)	XXXX	XX (X.X%)	X.XX (X.XX to X.XX)			X.XX (X.XX to X.XX)			X.XX (X.XX to X.XX)		
Underweight	XXXX	XX (X.X%)	XXXX	XX (X.X%)	XXXX	XX (X.X%)	X.XX (X.XX to X.XX)			X.XX (X.XX to X.XX)			X.XX (X.XX to X.XX)		
Change in weight-for- lenght z-score	XXXX	X.X (X.X)	XXXX	X.X (X.X)	XXXX	X.X (X.X)	X.X (X.X to X.X)			X.X (X.X to X.X)			X.X (X.X to X.X)		
Wasting	XXXX	XX (X.X%)	XXXX	XX (X.X%)	XXXX	XX (X.X%)	X.XX (X.XX to X.XX)			X.XX (X.XX to X.XX)			X.XX (X.XX to X.XX)		
Change in head circumference	XXXX	X.X (X.X)	XXXX	X.X (X.X)	XXXX	X.X (X.X)	X.X (X.X to X.X)			X.X (X.X to X.X)			X.X (X.X to X.X)		
Laboratory indices															
Anaemia	XXXX	XX (X.X%)	XXXX	XX (X.X%)	XXXX	XX (X.X%)	X.XX (X.XX to X.XX)			X.XX (X.XX to X.XX)			X.XX (X.XX to X.XX)		
Iron deficient	XXXX	XX (X.X%)	XXXX	XX (X.X%)	XXXX	XX (X.X%)	X.XX (X.XX to X.XX)			X.XX (X.XX to X.XX)			X.XX (X.XX to X.XX)		
Iron deficient anaemia	XXXX	XX (X.X%)	XXXX	XX (X.X%)	XXXX	XX (X.X%)	X.XX (X.XX to X.XX)			X.XX (X.XX to X.XX)			X.XX (X.XX to X.XX)		

MNPs, multiple micronutrient powders; CI, confidence interval *Values are mean (SD) or no. (%), with the exception of ferritin which is median (25th to 75th percentile). †Multiplicity-adjusted according to the pre-specified multiple testing strategy.

Continuous key secondary, secondary, and exploratory outcomes will be analysed similarly as the primary outcome. Ferritin (µg/L) will be log
_e_ transformed before analysis. Binary outcomes will be analysed using a generalised linear mixed model with a log-link function and binomial distribution, including child as a random intercept. In case of non-convergence, we will use a logit link function instead.

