		Due to bloody stool	XXX (XX.X)	XXX (XX.X)	XXX (XX.X)	0.XXX	0.XXX	0.XXX
		Due to vomiting	XXX (XX.X)	XXX (XX.X)	XXX (XX.X)	0.XXX	0.XXX	0.XXX
		Due to cough/ difficulty breathing	XXX (XX.X)	XXX (XX.X)	XXX (XX.X)	0.XXX	0.XXX	0.XXX
		Due to other ‡	XXX (XX.X)	XXX (XX.X)	XXX (XX.X)	0.XXX	0.XXX	0.XXX
	Extended follow-up period							
		Any reason	XXX (XX.X)	XXX (XX.X)	XXX (XX.X)	0.XXX	0.XXX	0.XXX
		Due to fever	XXX (XX.X)	XXX (XX.X)	XXX (XX.X)	0.XXX	0.XXX	0.XXX
		Due to diarrhea	XXX (XX.X)	XXX (XX.X)	XXX (XX.X)	0.XXX	0.XXX	0.XXX
		Due to bloody stool	XXX (XX.X)	XXX (XX.X)	XXX (XX.X)	0.XXX	0.XXX	0.XXX
		Due to vomiting	XXX (XX.X)	XXX (XX.X)	XXX (XX.X)	0.XXX	0.XXX	0.XXX
		Due to cough/ difficulty breathing	XXX (XX.X)	XXX (XX.X)	XXX (XX.X)	0.XXX	0.XXX	0.XXX
		Due to other ‡	XXX (XX.X)	XXX (XX.X)	XXX (XX.X)	0.XXX	0.XXX	0.XXX
	Study period							
		Any reason	XXX (XX.X)	XXX (XX.X)	XXX (XX.X)	0.XXX	0.XXX	0.XXX
		Due to fever	XXX (XX.X)	XXX (XX.X)	XXX (XX.X)	0.XXX	0.XXX	0.XXX
		Due to diarrhea	XXX (XX.X)	XXX (XX.X)	XXX (XX.X)	0.XXX	0.XXX	0.XXX
		Due to bloody stool	XXX (XX.X)	XXX (XX.X)	XXX (XX.X)	0.XXX	0.XXX	0.XXX
		Due to vomiting	XXX (XX.X)	XXX (XX.X)	XXX (XX.X)	0.XXX	0.XXX	0.XXX
		Due to cough/ difficulty breathing	XXX (XX.X)	XXX (XX.X)	XXX (XX.X)	0.XXX	0.XXX	0.XXX
		Due to other ‡	XXX (XX.X)	XXX (XX.X)	XXX (XX.X)	0.XXX	0.XXX	0.XXX

MNPs, multiple micronutrient powders; SAE, serious adverse event. Intervention period – 0–3 months, Extended follow-up period 4–12 months, Study period 0–12 months. *Hospitalisation is defined as an overnight stay. †Clinic visit is defined as visit to the clinic not resulting in hospitalisation. ‡Other is defined as stool with mucous, runny nose, skin problem, eye problem, oral problem, ear problem, constipation, check up, other.

C-reactive protein levels will be analysed using similar models as those described for the primary outcome and for inflammation similar models to those described for the binary key secondary and secondary outcomes.

We will present the multiplicity unadjusted P-Values for the safety outcomes, no multiple testing adjustment is planned.

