### Changes from the registry and published study protocol

This paper includes changes to the statistical analysis plan of the BRISC trial in the registry (registered May 2017) and protocol paper (accepted September 2017). These changes are:

The register states that the regression models will incorporate key confounders and unbalanced baseline factors into the model. Instead, the primary analysis model will include the stratification factors used during the randomisation and additional models (sensitivity analyses) will incorporate key confounders, or key confounders and unbalanced baseline factors. The protocol states on the topic of:Multiple testing: We detailed a multiple testing procedure for the primary and key secondary outcomes, thus the confidence level for the associated two-sided confidence interval will be less than 5% for some treatment effects.Analysis of binary outcomes: We changed the analysis model from generalised estimating equations to a mixed model.

This paper documents version 1 of the statistical analysis plan dated April 20, 2020. Any changes to this version between publishing and breaking of the code will be tracked and still considered as planned analyses. The statistical analysis plan will be approved during the blinded data review before breaking of the allocation code. Any changes after this signed version will be considered post-hoc.

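### The non-convergence fallback for binary outcomes replaces a risk ratio with a child-specific odds ratio, so entries in Table 2 could be on different, unlabelled scales

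*SAP article*

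**What the plan says.** The model is set in the SAP section on the analysis of efficacy outcomes: "Binary outcomes will be analysed using a generalised linear mixed model with a log-link function and binomial distribution, including child as a random intercept". The next sentence gives the fallback: "In case of non-convergence, we will use a logit link function instead". Only the link is replaced; the random intercept stays.

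The rule covers six secondary outcomes at month 3 and month 12. Three are anthropometric (stunting, underweight, wasting) and three are laboratory diagnoses (anaemia, iron deficiency, iron deficiency anaemia). The safety section extends it to inflammation: "for inflammation similar models to those described for the binary key secondary and secondary outcomes".

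The SAP names no effect measure for these outcomes. Table 2 reports them under a column headed Estimate (CI). Its footnote explains the arm summaries ("Values are mean (SD) or no. (%), with the exception of ferritin which is median (25th to 75th percentile") and the multiplicity mark, and nothing else. Table 3, by contrast, states that its ratio is an incidence rate ratio.

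On inference for these outcomes the section on multiple testing says: "No multiplicity adjustment is planned for secondary and exploratory outcomes, and no P-Values will be presented". On the departure from the protocol, the section on changes says: "We changed the analysis model from generalised estimating equations to a mixed model".

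**The concern.** The link decides what the treatment coefficient means. Exponentiated, it is a risk ratio under the log link. Under the logit link with a child random intercept it is an odds ratio for a given child, which is neither a risk ratio nor a population-average odds ratio.

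The SAP gives no step that converts the logit result back to a risk ratio, and no rule that holds one scale across outcomes, visits or analyses. Convergence is met or missed model by model. Anaemia could therefore be a risk ratio and stunting an odds ratio in the same column. The sensitivity analyses refit the models with extra covariates, in multiply imputed data and in the per-protocol population, so a main result and its own sensitivity analysis could differ because the scale changed and not because the data did. If only some imputed data sets failed to converge, the estimates to be pooled by Rubin's rules would not even be on one scale.

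These outcomes carry no P-values, so the estimate and its interval are the whole comparative result. Anaemia and iron deficiency prevalence are named in the trial's secondary objectives.

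**Working it through.** The SAP states no figure on this point, so there is none to reproduce. The check has three parts. All risks, risk ratios and random-intercept SDs below are assumptions, because the SAP gives none. The 40% and 20% risks are the anaemia thresholds for the WHO recommendations quoted in the Introduction; 5% stands for a rare outcome.

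**1. What each link estimates.** Let the random intercept be s·z, with z standard normal and independent of arm, and let a0 and a1 be the linear predictors for placebo and active.
- Log link: marginal risk = E[exp(a + s·z)] = exp(a + s²/2). The ratio of the two marginal risks is exp(a1 − a0), so the child-specific and population risk ratios coincide.
- Logit link: marginal risk = ∫ expit(a + s·z) φ(z) dz. Here exp(a1 − a0) is the child-specific odds ratio, and it differs from the marginal odds ratio whenever s > 0 and there is an effect.

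**2. Size of the change.** Fix the placebo risk p0 and the risk ratio at 0.75, so p1 = 0.75·p0. For p0 = 0.40, p1 = 0.30 and the marginal odds ratio is (0.30/0.70)/(0.40/0.60) = 0.643. For the child-specific odds ratio, solve the integral for a0 and a1 so that it returns p0 and p1 (80-point Gauss-Hermite quadrature), then take exp(a1 − a0).

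| Placebo risk | Risk ratio | Marginal OR | Child-specific OR, s = 1 | s = 2 | s = 3 |
|---|---|---|---|---|---|
| 5% | 0.75 | 0.74 | 0.73 | 0.68 | 0.62 |
| 20% | 0.75 | 0.71 | 0.67 | 0.59 | 0.51 |
| 40% | 0.75 | 0.64 | 0.59 | 0.49 | 0.39 |

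Each row describes the same two population risks. To place the SDs: the within-child correlation on the latent logit scale is s²/(s² + π²/3), which gives 1/4.29 = 0.23, 4/7.29 = 0.55 and 9/12.29 = 0.73.

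**3. Is non-convergence plausible?** Under the log link a child's risk exceeds 1 when s·z > −a. With marginal risk p0, a = ln(p0) − s²/2. For p0 = 0.40 and s = 1, a = −0.916 − 0.5 = −1.416, and P(z > 1.416) = 0.078. The nominal shares are:

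| Marginal risk | s = 0.5 | s = 1 | s = 1.5 |
|---|---|---|---|
| 20% | 0.0% | 1.7% | 3.4% |
| 40% | 1.9% | 7.8% | 8.7% |

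These are indicative only: the formula counts the impossible risks above 1 towards the marginal risk, and no model was fitted or simulated. They show that the model does not respect the upper bound for common outcomes, which makes fitting trouble plausible. They do not show that it will occur.

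**The case against.** The strongest defence is that trigger and consequence are both fixed before unblinding: one model, one trigger, one fallback. That stands. A reader might infer that the analyst could pick the more favourable scale after seeing the data; the SAP leaves no such discretion. The fault is that a pre-specified rule changes the quantity estimated.

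Second, the reach is limited. The primary outcome and all key secondary outcomes are continuous, and the binary efficacy rows carry no tests. That also stands. Inflammation is not a row of Table 2, so it adds nothing to the mixed-column problem, although it inherits the fallback.

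Third, Table 2 prints the count and percentage by arm, so a reader can form a crude risk ratio for any row. This softens the problem, and it tells against inferring that the trial will grossly overstate its effects: an odds ratio misleads only if it is read as a risk ratio. But the crude ratio is unadjusted, uses observed cases only and comes without an interval, so it does not replace the planned estimate.

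Fourth, Table 2 already mixes scales: mean changes, log-transformed ferritin, binary outcomes. True, but those differences follow the type of outcome. Here two rows of the same type could differ with nothing to show it.

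Fifth, it is tempting to say that non-convergence is to be expected. The documents do not support that. The SAP allows for it, and the calculation makes it plausible. Likewise 40% is a policy threshold and not this trial's prevalence, and the lowest figure, 0.39, needs a random-intercept SD of 3.

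**Conclusion.** The point holds, within limits. If the log-link model fails, the SAP as written reports a child-specific odds ratio where it would otherwise report a risk ratio, and nothing in the document converts, aligns or labels the two.

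The size depends on how common the outcome is and how much children vary. For a risk ratio of 0.75 the gap is slight for a rare outcome with little between-child variation (0.73 at 5% risk, SD 1) and large for a common, strongly correlated one (0.49 at 40%, SD 2). The figures assume a normal random intercept that has the same SD in both arms and is independent of treatment.

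The point bears on how secondary binary outcomes and inflammation are reported and compared. It does not touch the primary outcome, the formal tests or the multiplicity scheme. It goes beyond a missing label, because the stated rule itself produces the inconsistency and a fallback that keeps the measure is available.

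**What to change.** State that the target measure for binary outcomes is the risk ratio, whichever link is fitted. Keep the logit link as the fallback, but when it is used, report the population-average risk ratio from it. For each arm and visit, average the predicted risk over the observed covariates and integrate over the fitted random-intercept distribution. Take ratios between arms, with a delta-method or bootstrap interval. Apply the same rule to inflammation, to every sensitivity refit and within each imputed data set before pooling. Name the measure in the Table 2 footnote and mark the rows that used the fallback. This keeps the likelihood-based handling of missing data under MAR that the SAP makes its primary strategy.

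The cost is modest programming: 6 outcomes × 2 visits × 3 comparisons = 36 main estimates in Table 2, plus inflammation and the refits.

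A log-link Poisson model with child-clustered robust standard errors also keeps the risk ratio. But it gives up the likelihood-based MAR handling and moves back towards the estimating-equation approach that the SAP replaced. It should be a last resort only, with that cost stated.

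The SAP allows tracked changes until the allocation code is broken. After the signed version, the change would have to be reported as post hoc.

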### Safety outcomes: analysis

The total number of times at least one infection (fever, diarrhoea, bloody stool, vomiting, cough/ difficulty breathing) was reported will be summarised per infection type during the intervention period (weekly reports), extended follow-up period (monthly reports), and (total) study period. The incidence rate ratio will be estimated using a Poisson regression model, with a logarithm of the time at risk as offset (
Table 3).

**Table 3. T3:** Infectious morbidity, according to treatment group (safety population).

	Period	Iron *	MNPs *	Placebo *	Iron vs. Placebo		MNPs vs. Placebo		Iron vs. MNPs	
		(N=XXXX)	(N=XXXX)	(N=XXXX)	Ratio † (95% CI)	P Value	Ratio † (95% CI)	P Value	Ratio † (95% CI)	P Value
Fever - total number of times reported	Intervention period	XX (X-XX)	XX (X-XX)	XX (X-XX)	X.XX (X.XX to X.XX)	0.XXX	X.XX (X.XX to X.XX)	0.XXX	X.XX (X.XX to X.XX)	0.XXX
	Extended follow-up period	X (X-X)	X (X-X)	X (X-X)	X.XX (X.XX to X.XX)	0.XXX	X.XX (X.XX to X.XX)	0.XXX	X.XX (X.XX to X.XX)	0.XXX
	Study period	XX (X-XX)	XX (X-XX)	XX (X-XX)	X.XX (X.XX to X.XX)	0.XXX	X.XX (X.XX to X.XX)	0.XXX	X.XX (X.XX to X.XX)	0.XXX
Diarrhea - total number of times reported	Intervention period	XX (X-XX)	XX (X-XX)	XX (X-XX)	X.XX (X.XX to X.XX)	0.XXX	X.XX (X.XX to X.XX)	0.XXX	X.XX (X.XX to X.XX)	0.XXX
	Extended follow-up period	X (X-X)	X (X-X)	X (X-X)	X.XX (X.XX to X.XX)	0.XXX	X.XX (X.XX to X.XX)	0.XXX	X.XX (X.XX to X.XX)	0.XXX
	Study period	XX (X-XX)	XX (X-XX)	XX (X-XX)	X.XX (X.XX to X.XX)	0.XXX	X.XX (X.XX to X.XX)	0.XXX	X.XX (X.XX to X.XX)	0.XXX
Bloody stool - total number of times reported	Intervention period	XX (X-XX)	XX (X-XX)	XX (X-XX)	X.XX (X.XX to X.XX)	0.XXX	X.XX (X.XX to X.XX)	0.XXX	X.XX (X.XX to X.XX)	0.XXX
	Extended follow-up period	X (X-X)	X (X-X)	X (X-X)	X.XX (X.XX to X.XX)	0.XXX	X.XX (X.XX to X.XX)	0.XXX	X.XX (X.XX to X.XX)	0.XXX
	Study period	XX (X-XX)	XX (X-XX)	XX (X-XX)	X.XX (X.XX to X.XX)	0.XXX	X.XX (X.XX to X.XX)	0.XXX	X.XX (X.XX to X.XX)	0.XXX
Vomiting - total number of times reported	Intervention period	XX (X-XX)	XX (X-XX)	XX (X-XX)	X.XX (X.XX to X.XX)	0.XXX	X.XX (X.XX to X.XX)	0.XXX	X.XX (X.XX to X.XX)	0.XXX
	Extended follow-up period	X (X-X)	X (X-X)	X (X-X)	X.XX (X.XX to X.XX)	0.XXX	X.XX (X.XX to X.XX)	0.XXX	X.XX (X.XX to X.XX)	0.XXX
	Study period	XX (X-XX)	XX (X-XX)	XX (X-XX)	X.XX (X.XX to X.XX)	0.XXX	X.XX (X.XX to X.XX)	0.XXX	X.XX (X.XX to X.XX)	0.XXX
Cough/Difficulty breathing - total number of times reported	Intervention period	XX (X-XX)	XX (X-XX)	XX (X-XX)	X.XX (X.XX to X.XX)	0.XXX	X.XX (X.XX to X.XX)	0.XXX	X.XX (X.XX to X.XX)	0.XXX
	Extended follow-up period	X (X-X)	X (X-X)	X (X-X)	X.XX (X.XX to X.XX)	0.XXX	X.XX (X.XX to X.XX)	0.XXX	X.XX (X.XX to X.XX)	0.XXX
	Study period	XX (X-XX)	XX (X-XX)	XX (X-XX)	X.XX (X.XX to X.XX)	0.XXX	X.XX (X.XX to X.XX)	0.XXX	X.XX (X.XX to X.XX)	0.XXX

MNPs, multiple micronutrient powders; CI, confidence interval Intervention period – 0–3 months, Extended follow-up period 4–12 months, Study period 0–12 months. *Values are median (25th to 75th percentile). †Ratio is incidence rate ratio.

The number and percentage of children who died, had at least one (overnight) hospitalisation, reported at least one serious adverse event, and had at least one clinic visit (due to any infection, fever, diarrhoea, bloody stool, vomiting, cough/ difficulty breathing, other infection) during the intervention period, extended follow-up period, and study period will be reported and compared between treatments using a log-binomial regression model (
Table 4). 

**Table 4. T4:** Death, serious adverse events, hospitalisation, according to treatment group (safety population).

	Period		Iron (N=XXXX)	MNPs (N=XXXX)	Placebo (N=XXXX)	P-Value Iron vs. Placebo	P-Value MNPs vs. Placebo	P-Value Iron vs. MNPs
Children who died - no. (%)								
	Intervention period		XXX (XX.X)	XXX (XX.X)	XXX (XX.X)	0.XXX	0.XXX	0.XXX
	Extented follow-up period		XXX (XX.X)	XXX (XX.X)	XXX (XX.X)	0.XXX	0.XXX	0.XXX
	Study period		XXX (XX.X)	XXX (XX.X)	XXX (XX.X)	0.XXX	0.XXX	0.XXX
Children ≥1 hospitalisation * - no. (%)								
	Intervention period		XXX (XX.X)	XXX (XX.X)	XXX (XX.X)	0.XXX	0.XXX	0.XXX
	Extended follow-up period		XXX (XX.X)	XXX (XX.X)	XXX (XX.X)	0.XXX	0.XXX	0.XXX
	Study period		XXX (XX.X)	XXX (XX.X)	XXX (XX.X)	0.XXX	0.XXX	0.XXX
Children with ≥1 SAE - no. (%)								
	Intervention period		XXX (XX.X)	XXX (XX.X)	XXX (XX.X)	0.XXX	0.XXX	0.XXX
	Extented follow-up period		XXX (XX.X)	XXX (XX.X)	XXX (XX.X)	0.XXX	0.XXX	0.XXX
	Study period		XXX (XX.X)	XXX (XX.X)	XXX (XX.X)	0.XXX	0.XXX	0.XXX
Children ≥1 clinic visit † - no. (%)								
	Intervention period							
		Any reason	XXX (XX.X)	XXX (XX.X)	XXX (XX.X)	0.XXX	0.XXX	0.XXX
		Due to fever	XXX (XX.X)	XXX (XX.X)	XXX (XX.X)	0.XXX	0.XXX	0.XXX
		Due to diarrhea	XXX (XX.X)	XXX (XX.X)	XXX (XX.X)	0.XXX	0.XXX	0.XXX
		Due to bloody stool	XXX (XX.X)	XXX (XX.X)	XXX (XX.X)	0.XXX	0.XXX	0.XXX
		Due to vomiting	XXX (XX.X)	XXX (XX.X)	XXX (XX.X)	0.XXX	0.XXX	0.XXX
		Due to cough/ difficulty breathing	XXX (XX.X)	XXX (XX.X)	XXX (XX.X)	0.XXX	0.XXX	0.XXX
		Due to other ‡	XXX (XX.X)	XXX (XX.X)	XXX (XX.X)	0.XXX	0.XXX	0.XXX
	Extended follow-up period							
		Any reason	XXX (XX.X)	XXX (XX.X)	XXX (XX.X)	0.XXX	0.XXX	0.XXX
		Due to fever	XXX (XX.X)	XXX (XX.X)	XXX (XX.X)	0.XXX	0.XXX	0.XXX
		Due to diarrhea	XXX (XX.X)	XXX (XX.X)	XXX (XX.X)	0.XXX	0.XXX	0.XXX
		Due to bloody stool	XXX (XX.X)	XXX (XX.X)	XXX (XX.X)	0.XXX	0.XXX	0.XXX
		Due to vomiting	XXX (XX.X)	XXX (XX.X)	XXX (XX.X)	0.XXX	0.XXX	0.XXX
		Due to cough/ difficulty breathing	XXX (XX.X)	XXX (XX.X)	XXX (XX.X)	0.XXX	0.XXX	0.XXX
		Due to other ‡	XXX (XX.X)	XXX (XX.X)	XXX (XX.X)	0.XXX	0.XXX	0.XXX
	Study period							
		Any reason	XXX (XX.X)	XXX (XX.X)	XXX (XX.X)	0.XXX	0.XXX	0.XXX
		Due to fever	XXX (XX.X)	XXX (XX.X)	XXX (XX.X)	0.XXX	0.XXX	0.XXX
		Due to diarrhea	XXX (XX.X)	XXX (XX.X)	XXX (XX.X)	0.XXX	0.XXX	0.XXX
		Due to bloody stool	XXX (XX.X)	XXX (XX.X)	XXX (XX.X)	0.XXX	0.XXX	0.XXX
		Due to vomiting	XXX (XX.X)	XXX (XX.X)	XXX (XX.X)	0.XXX	0.XXX	0.XXX
		Due to cough/ difficulty breathing	XXX (XX.X)	XXX (XX.X)	XXX (XX.X)	0.XXX	0.XXX	0.XXX
		Due to other ‡	XXX (XX.X)	XXX (XX.X)	XXX (XX.X)	0.XXX	0.XXX	0.XXX

MNPs, multiple micronutrient powders; SAE, serious adverse event. Intervention period – 0–3 months, Extended follow-up period 4–12 months, Study period 0–12 months. *Hospitalisation is defined as an overnight stay. †Clinic visit is defined as visit to the clinic not resulting in hospitalisation. ‡Other is defined as stool with mucous, runny nose, skin problem, eye problem, oral problem, ear problem, constipation, check up, other.

C-reactive protein levels will be analysed using similar models as those described for the primary outcome and for inflammation similar models to those described for the binary key secondary and secondary outcomes.

We will present the multiplicity unadjusted P-Values for the safety outcomes, no multiple testing adjustment is planned.

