### General principles

The intention-to-treat population will be used for the analysis of all primary, key secondary, secondary, and exploratory outcomes and will include all children who were randomised. In case of missing outcome data, we will follow the missing data handling strategy outlined below. The safety population will be used for the analysis of all safety outcomes and consists of all children who received at least one study treatment (including control). Children who have withdrawn informed consent for use of all their data will be excluded from all analyses. Children will be reported and analysed according to their randomised treatment allocation. Time-windows will be applied to all visit-wise data collected at baseline, month 3, and month 12, with assessments outside the predefined visit windows excluded from the analyses. Outcomes will be summarised using frequencies and percentages (based on the non-missing sample size) for categorical variables, mean and standard deviation for continuous variables, or median and quartiles (25th and 75th percentile) for non-symmetrical continuous variables. All analyses models will be adjusted for the stratification variables used during the randomisation (union and sex). All confidence intervals and P-Values will be two-sided.

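### The Table 3 infection rate ratios come from plain Poisson regression on repeated yes/no reports per child, so their confidence intervals and P-values do not reflect the true between-child variance

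*SAP article*

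**What the plan says.** Under Outcome variables, infection data were "collected weekly during the intervention period and monthly during the follow-up period". Under Safety outcomes: analysis, the number of times each infection type was reported is summarised "during the intervention period (weekly reports), extended follow-up period (monthly reports), and (total) study period", and then: "The incidence rate ratio will be estimated using a Poisson regression model, with a logarithm of the time at risk as offset".

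The Table 3 footnote reads "Values are median (25th to 75th percentile). †Ratio is incidence rate ratio". A median and quartiles within each arm only make sense for a count per child, so the modelled outcome is a repeated-event count per child. Table 3 gives every ratio a 95% confidence interval and a P-value, for five symptoms, three periods and three pairwise comparisons.

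General principles adds union and sex to all models. No other covariate, variance option or fallback is given for these counts. By contrast, the efficacy section gives the continuous outcomes an unstructured covariance, and the binary outcomes a random intercept for child with a fallback if the model does not converge.

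**The concern.** A Poisson model takes the variance of each child's count to equal its mean, given the covariates. Two features of these counts break that assumption, in opposite directions. Some children are ill repeatedly and others hardly at all, which pushes the variance above the mean. Each report is yes or no, so a count cannot exceed the number of reports, which pushes the variance below the mean when symptoms are common. Only by coincidence would the two cancel. Adjusting for union and sex does not remove the remaining differences between children.

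Infection is the harm that the Introduction raises for iron, and infection risk is among the secondary objectives in Aims. If the intervals are too narrow, chance differences in fever, diarrhoea or cough can look like a harm or a benefit. If they are too wide, a real excess can be missed.

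**Working it through.** The plan states no event rate, dispersion or power for these outcomes, so there is no figure to reproduce. The check asks how far a Poisson standard error is off under stated assumptions.

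**Inputs.** From the document: weekly reports for 3 months, so m = 3 × 52/12 = 13; monthly reports for 9 months, so m = 9; 1100 children per arm; two-sided 95% intervals. Assumed: probability p that a report is positive, and within-child correlation ICC between reports.

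**Formulas.** For m yes/no reports with common correlation, variance/mean is φ = (1 − p)(1 + (m − 1) × ICC). The true standard error of the log rate ratio is √φ times the Poisson one, so the reported standard error is too small by 1 − 1/√φ. The true size of a nominal 5% test is 2 × Φ(−1.96/√φ).

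**Results for m = 13.**

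| p | ICC | φ | True SE larger by | Reported SE too small by | Type I error |
|---|---|---|---|---|---|
| 0.2 | 0.05 | 0.8 × 1.6 = 1.28 | 13% | 12% | 8.3% |
| 0.2 | 0.1 | 0.8 × 2.2 = 1.76 | 33% | 25% | 14.0% |
| 0.2 | 0.2 | 0.8 × 3.4 = 2.72 | 65% | 39% | 23.5% |
| 0.1 | 0.05 | 0.9 × 1.6 = 1.44 | 20% | 17% | 10.2% |
| 0.1 | 0.1 | 0.9 × 2.2 = 1.98 | 41% | 29% | 16.4% |
| 0.1 | 0.2 | 0.9 × 3.4 = 3.06 | 75% | 43% | 26.3% |

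**Direction.** φ = 1 at ICC = p/((1 − p)(m − 1)). For m = 13 this is 0.2/(0.8 × 12) = 0.021 at p = 0.2 and 0.5/(0.5 × 12) = 0.083 at p = 0.5. Above the break-even value the Poisson intervals are too narrow, below it too wide. At p = 0.3 and ICC 0, φ = 0.7 and the error is 1.9%.

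**Simulation.** Two arms of 1100, no true effect, beta-binomial counts, 4000 replicates, Wald test.

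| m | p | ICC | φ | Error, Poisson SE | Error, robust SE |
|---|---|---|---|---|---|
| 13 | 0.2 | 0 | 0.80 | 3.1% | 5.4% |
| 13 | 0.2 | 0.05 | 1.28 | 9.0% | 5.3% |
| 13 | 0.2 | 0.1 | 1.76 | 13.1% | 4.5% |
| 13 | 0.2 | 0.2 | 2.72 | 22.8% | 5.0% |
| 13 | 0.05 | 0.1 | 2.09 | 16.9% | 5.1% |
| 9 | 0.4 | 0.05 | 0.84 | 3.0% | 4.9% |
| 9 | 0.4 | 0.1 | 1.08 | 6.3% | 5.2% |
| 9 | 0.4 | 0.2 | 1.56 | 11.9% | 5.1% |

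A robust variance holds the error near 5% in every case, whether the counts are over- or under-dispersed.

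**Whole-study row (secondary).** This row adds about 13 weekly and 9 monthly reports over one time offset. Suppose that a monthly report covers the whole month, that weeks are independent, and that a weekly risk ratio of 1.20 persists for all 12 months. The monthly risk is then 1 − (1 − p)^(52/12). With equal follow-up the offset cancels:

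- p = 0.15: monthly risks 0.577 and 0.506; ratio (13 × 0.18 + 9 × 0.577)/(13 × 0.15 + 9 × 0.506) = 1.16.
- p = 0.30: monthly risks 0.855 and 0.787; ratio (13 × 0.36 + 9 × 0.855)/(13 × 0.30 + 9 × 0.787) = 1.13.

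**The case against.** The best defence is that these are safety outcomes with unadjusted P-values. They lie outside the gatekeeping procedure and cannot decide whether the trial met its primary objective. The article also provides for a final plan to be signed at the blinded data review, so an analyst could still choose a suitable variance. The first part is right and limits the consequences. The second does not answer the point: the article presents itself as version 1 of the SAP, it specifies within-child dependence for the other repeated outcomes, and it treats changes after sign-off as post-hoc.

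It is also fair to say that the size rests wholly on assumed rates and correlations. That stands, and it rules out several stronger readings that a reader might infer:

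- *All safety intervals are wrong.* The problem is confined to Table 3. Deaths, hospitalisations, serious adverse events and clinic visits are analysed as one yes/no per child per period by log-binomial regression. C-reactive protein and inflammation use the longitudinal models.
- *The intervals are always too narrow.* Capped counts with weak clustering give the opposite error.
- *The number of false positives in Table 3 can be stated.* The table has 5 × 3 × 3 = 45 P-values, but the errors of 8 to 26% are for 13-report counts only. The monthly and pooled rows behave differently, and no rates are given for any row.
- *The whole-study ratio is biased by a known amount.* The 1.13 to 1.16 needs full-month recall, independent weeks and an effect lasting nine months after treatment. The document states none of these, and independent weeks do not sit with the correlations assumed for the variance. Separate rows for the two periods are already planned, so no reader depends on the pooled row alone.

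**Conclusion.** The point holds for the confidence intervals and P-values in Table 3. As written, the model fixes the variance at the Poisson value for counts that have no reason to follow it, and nothing else in the plan repairs this. With 13 weekly reports, p of 0.1 to 0.2 and ICC of 0.05 to 0.2, all assumed, the variance is 1.3 to 3.1 times Poisson, true standard errors are 13 to 75% larger than reported, and type I error is about 8 to 26% instead of 5%. Modest clustering is enough to make the intervals too narrow, and the reverse error needs common symptoms and very weak clustering. The single-period point estimates do not depend on the variance choice.

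The whole-study row is a lesser and conditional matter. Weekly and monthly reports are different units, and if a monthly report covers the whole month the pooled ratio can be pulled towards 1.

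**What to change.** State in the safety analysis section that the Table 3 Poisson models, with the offset and the union and sex adjustment already planned, will use robust (sandwich) standard errors. This corrects over- and under-dispersion alike. A negative binomial model would allow only for over-dispersion. The change costs one sentence and one software option, needs no new data and leaves the rate ratios as they are. The intervals will usually be wider. It should be in the version signed before the allocation code is broken.

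For the whole-study row, either name the two separate-period rows as the main result and label the pooled row descriptive, or replace it with a model on individual reports (symptom yes/no per completed report) that has a term for reporting interval and is clustered on child. The first option costs one sentence; the second needs one additional model per symptom.
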